### 2.4. Study Assessment Instruments

For this protocol, we use the following instruments:

(1) Sociodemographic and Clinical Questionnaire: This questionnaire was developed for this study to assess the following sociodemographic variables: age, education, religion, origin, race, marital status, occupation, and participants’ monthly income. It also assesses the following clinical variables: patient age, diagnosis, staging, and types of treatment, which are obtained from patients’ medical records.

(2) McGill Quality of Life Questionnaire [17]: This 16-item questionnaire is divided into domains such as physical well-being, psychological well-being, existential well-being, support, and physical symptoms. It presents a single-item scale that measures overall quality of life, which is not included in the total score but rather is used for comparison. There is also an open-ended question in which patients can list the things that have had the greatest effect on their quality of life. The scale has 11 points, ranging from 0 to 10. A higher final score indicates a better quality of life.

(3) Brief Pain Inventory (Reduced Version) [18]: This questionnaire uses a body diagram on which patients can mark the location of their pain. There are also eight questions about pain intensity on a scale from 0 to 10. A higher inventory score indicates worse pain intensity.

(4) Hospital Anxiety and Depression Scale (HADS) [19]: This is a 14-item instrument with two subscales, one for anxiety and one for depression, each with 7 items. Each item’s score can range from 0 to 3, with a maximum score of 21 points for each subscale. Patients without anxiety or depression are considered to have a score from 0 to 8, while those with a score of 9 or higher are considered to have anxiety or depression

(5) Edmonton Symptom Assessment Scale (ESAS) [20]: This is a self-report questionnaire designed to measure both objective and subjective symptoms. In this scale, patients or their caregivers/family members assign a score from 0 to 10 to each symptom, with 0 representing the absence and 10 representing the highest intensity of the symptom.

(6) National Comprehensive Cancer Network^®^ (NCCN) Distress Thermometer [21]: This is administered in the form of a questionnaire during the three designated moments. This instrument, which has been translated and validated by the NCCN, is utilized to assess the psychological well-being of individuals diagnosed with cancer.

In each interview (T1, T2, and T3), all questionnaires are administered before the meditation session (Before Meditation), and only the ESAS is administered immediately after the meditation session (After Meditation) to capture acute changes in symptoms. All assessment instruments are based on questionnaires and assessment scales already validated in the literature and are listed in Table 2.

### 2.5. Interventions

The study is conducted at three moments (T1, T2, and T3) with all study groups (case group—Group A; active control group—Group B; passive control group—Group C). In T1 of the study, all groups respond to the baseline assessment approach of the study, which consists of a sociodemographic and clinical questionnaire for the three groups. The data is collected at the FCECON office, immediately after these patients have completed their medical appointment at the Pain Therapy and Palliative Care Service at FCECON.

Participants are randomized into three groups: a case group with guided meditation using virtual reality/3D (three-dimensional) video (Group A), an active control group with guided meditation using 2D (two-dimensional) video (Group B), and a passive control group with guided meditation using audio (Group C). All participants are interviewed at three moments: time 1 (T1)—the first day of intervention and collection of instruments; time 2 (T2)—four weeks after T1; time 3 (T3)—eight weeks after T1.

In all groups and at all moments, T1, T2, and T3, patients respond to the sociodemographic and clinical questionnaire and other instruments measuring quality of life, psychological morbidity, pain, and symptoms. After completing the meditation, patients respond to the Edmonton Symptom Assessment Scale.

The randomization sequence and the type of meditation used in each group at the FCECON office are accessible to the research team, but participants are not aware of the other research groups or the type of meditation is used in each group. Data collection takes place separately on different days and at different times, without one participant having access to another’s meditation.

Subsequently to the in-person intervention at the FCECON office, participants from all three groups receive standardized instructions for conducting home meditation. The practice should be conducted using a video previously provided by the research team, accessed on the participants’ own cell phones, without the need for an internet connection, in offline mode.

The content of the home meditation consists of the same 2D video with guided meditation audio for Groups A and B and Group C receives only audio for guided meditation. In order to promote adherence to the protocol, all participants receive standardized reminders on their mobile devices requesting that they perform the meditation on Mondays and Thursdays between 9 am and 10 am during the eight weeks of the experimental protocol.

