### 2.3. Recruitment and Participants

The protocol includes patients between the ages of 18 and 75 who are assisted at the STDCP, with a diagnosis of cancer pain; who can understand Portuguese, have normal vision and hearing, can move their heads, and have sufficient motor control to perform bodily movements; who have a mobile phone with a compatible system; and who agree to participate in the study and sign the informed consent form (ICF).

Indigenous patients were excluded from study due to cultural peculiarities, language, and special legislation. The other exclusion criteria are patients with a history of serious mental illness (DSM-5, Diagnostic and Statistical Manual of Mental Disorders—schizophrenia, schizotypal disorders, delusional disorders, borderline personality disorder, manic phase in bipolar disorder, and dementia); neurological deficits that compromise the degree of cooperation (Glasgow Coma Scale ≥ 14); impaired comprehension and communication skills based on the researcher’s assessment; reports of discomfort when using immersive virtual reality; disease progression that limits regular outpatient mobility; and patients with brain tumors, brain metastases, metastatic lung neoplasm, or a history of seizures.

In order to participate in the study, patients are required to provide informed consent. The consent document includes a comprehensive explanation of the study’s objectives, its potential risks and benefits, and the various stages of the research process. The subjects are then requested to provide their consent and written informed consent is then obtained from all participants.

The protocol stipulates that harm will be defined if any adverse effect occurs after randomization of study participants. The harm will be evaluated systematically at all time points of the study (T1, T2, T3) through the use of structured questionnaires and symptom scales, as well as non-systematically through spontaneous reports from participants. All events will be documented, and serious adverse events will be reported to the ethics committee, as required by Brazilian ethical standards. The ICH Good Clinical Practice (ICH-GCP) definitions will be used to categorize all adverse events.

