#### 2.5.4. Randomization and Blinding

The randomization is performed by the principal investigator using a specific commercial mobile application called Randomizer^®^ for Clinical Trial Lite, which is a secure, validated application that works with encrypted network traffic using TLS (Transport Layer Security), a strong encryption for random distribution among the research groups.

The study is a comparative study; the participants in the case group, active control group, and passive control group are recruited in the same way, receive the same information about meditation, and answer the same questionnaires before and after meditation. However, given the nature of behavioral interventions (virtual reality and 2D video or audio), both participants and research assistants conducting the interventions cannot be blinded to group allocation. The questionnaires used in the study are administered and collected by researchers who are aware of the intervention modality and are responsible for setting up the equipment, training participants, and providing technical support.

To minimize bias, the statistician responsible for the analyses will remain blinded to group allocation, and group labels will be coded during data analysis. We recognize the lack of blinding of the evaluator as a limitation, which will be considered in the interpretation of the results.

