### 2.6. Outcome Measures

The primary outcome of the protocol is the change in pain intensity, measured by the Brief Pain Inventory—Short Form (BPI), from the beginning of the study (T1) to the eight-week follow-up (T3). The item “worst pain in the last 24 h” (numerical scale from 0 to 10) will be used as the indicator of pain intensity, as it has been validated and demonstrated to be clinically important in oncology and palliative care populations.

Secondary outcomes will encompass metrics designed to assess the psychological, functional, and symptomatic domains. Psychological morbidity will be assessed using the Hospital Anxiety and Depression Scale (HADS), including total and subscale scores. Quality of life will be evaluated using the McGill Quality of Life Questionnaire.

In addition to longitudinal assessments at T1 (baseline), T2 (four weeks), and T3 (eight weeks), the immediate pre- and post-intervention effects will be explored using the Edmonton Symptom Assessment Scale (ESAS). The ESAS will be administered prior to and following each in-person guided meditation session to assess acute changes in symptoms. Pain intensity, severity, and interference will be measured using the respective subscales of the BPI. The extent to which participants adhere to the intervention will be determined by calculating the percentage of prescribed meditation sessions completed during the follow-up period.

The subsequent Table 3 offers a synopsis of all outcome measures, variables, analysis metrics, aggregation methods, and assessment time points.

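### Baseline pain is taken straight after the pain-service appointment and every arm meditates, so within-arm T1-to-T3 change cannot be read as a meditation effect; the between-arm comparison loses precision but is not biased

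*Protocol article*

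**What the plan says.** Section 2.5 places T1 data collection at the FCECON office, "immediately after these patients have completed their medical appointment at the Pain Therapy and Palliative Care Service". Section 2.4 and Table 2 put the Brief Pain Inventory among the instruments completed at that visit before meditation. Under Section 2.6 the primary outcome is the change from T1 to T3 (eight weeks) in the BPI worst-pain item, scored 0 to 10 with a 24-hour recall.

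Section 2.3 admits "patients between the ages of 18 and 75 who are assisted at the STDCP, with a diagnosis of cancer pain". Its detailed inclusion and exclusion lists do not mention recent treatment changes or separate first consultations from established follow-up. The clinical questionnaire in Section 2.4 takes types of treatment from the medical record; whether or when treatment changed is not among the items listed. Table 3 has no such variable either.

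"Participants are randomized into three groups" (Section 2.5), and each group receives a form of guided meditation. Section 2.5.4 says that participants in all groups "are recruited in the same way, receive the same information about meditation, and answer the same questionnaires before and after meditation". Section 3.2 compares the groups over time, but it also gives the repeated-measures ANOVA the task of establishing the effect of each intervention. Section 5 anticipates strong evidence for adding mindfulness meditation to pain management in palliative care.

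**The concern.** A pain-service consultation is a natural occasion for adjusting treatment. If it is adjusted, the T1 score reflects the regimen in place beforehand, because the item asks about the previous 24 hours. The T2 and T3 scores reflect the regimen afterwards. The change from T1 to T3 in any one arm then contains the response to that adjustment, together with regression to the mean and the course of the disease.

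This matters here because no arm goes without meditation. The contrasts between arms compare formats (immersive video, 2D video, audio). They do not isolate meditation from no meditation. A conclusion about meditation itself, such as Section 5 foresees, could rest only on within-arm change, which cannot carry it. For the between-arm comparison, a mixture of recently changed and unchanged patients adds variance to the outcome.

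**Working it through.** **Inputs from the article.** T1 follows the appointment (2.5). The primary item has a 24-hour recall and is analysed as T1-to-T3 change (2.6). There are three meditation arms (2.5) and 39 patients per arm before allowance for loss (3.1). The article gives no figure for how often treatment changes at the appointment, or for its effect on pain, so there is no stated figure to reproduce.

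**Assumed inputs, not in the article.** Pain SD 2.2 at each time; T1-T3 correlation 0.5; a share p of patients with treatment changed at T1; in those patients an extra fall with mean 2 points and SD 1.

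**1. Within-arm change with no meditation effect.** Expected change = -p × 2. The last column is the share of 8,000 simulated trials in which a paired test within Group A is significant at 5%.

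| p | Expected change | Simulated change | Falsely significant |
|---|---|---|---|
| 0.2 | -0.4 | -0.40 | 17% |
| 0.4 | -0.8 | -0.81 | 50% |
| 0.6 | -1.2 | -1.21 | 83% |

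**2. Between-arm bias.** With p equal across arms, the simulated A-minus-C difference stayed within 0.01 of zero. The three-arm test rejected in 4.5% to 5.1% of trials, so its error rate is held.

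**3. Between-arm precision.** Variance of change without treatment changes = 2 × 2.2² × (1 - 0.5) = 4.84, SD 2.20. The added variance is p × (1² + 2²) - (2p)². At p = 0.4 this is 0.4 × 5 - 0.64 = 1.36, so the total is 6.20 and the SD 2.49. With a true 1-point effect in Group A only and 39 per arm, simulated power of the three-arm test on change falls from 0.52 to 0.43 (0.40 at p = 0.6).

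**4. What a yes/no covariate could recover.** At p = 0.4 the part of the added variance explained by the flag is p(1 - p) × 2² = 0.96. The remaining 0.40 is variation in response among changed patients. The adjusted variance is 4.84 + 0.40 = 5.24, SD 2.29. If recorded accurately, the flag would remove 0.96/1.36 = 71% of the added variance.

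**5. Sensitivity to the assumptions.** With a residual SD of 2.5 (variance 6.25) and a fixed extra fall δ, the share of outcome variance due to this factor is p(1 - p)δ² / [6.25 + p(1 - p)δ²].

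| p | δ = 2 | δ = 3 |
|---|---|---|
| 0.2 | 9.3% | 18.7% |
| 0.3 | 11.8% | 23.2% |
| 0.5 | 13.8% | 26.5% |

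**The case against.** The strongest reply is that this is a randomized trial whose arms share one recruitment route, so same-day treatment changes are balanced in expectation. That stands. A reader might infer from the timing of T1 that the primary comparison is confounded; the documents do not support this. Bias between arms would need treatment changes to differ systematically by arm. In the simulation, shares of 0.5, 0.4 and 0.3 in A, B and C gave an A-minus-C bias of -0.4 points and a 9% false-positive rate, but nothing in the article says such a pattern occurs. Section 2.5 says that the research team can access the randomization sequence, without saying whether this is before enrolment. That is a separate question of allocation concealment.

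Nor is chance imbalance a bias. At p = 0.4 the standard error of the arm difference is 2.49 × √(2/39) = 0.56, against 2.20 × √(2/39) = 0.50 without the factor, so the usual test already allows for it.

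It is also fair to say that Table 3's primary row lists the final value and a mean difference as well as change from baseline, so the plan is not purely within-arm. The article never states that treatment is changed at the appointment, and its description of patients followed or monitored by the service suggests that many are established. Medical records are already a data source, so T1 status might be partly reconstructed later. Section 3.1 stresses limited recruitment, which makes entry under usual care a defensible choice. Section 4 already names concurrent drug therapy as a limitation.

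These replies narrow the point. They do not answer the wording of Sections 3.2 and 5, which invites a conclusion about meditation that only within-arm change could supply.

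**Conclusion.** The point holds in this limited form. Within-arm T1-to-T3 change cannot be attributed to meditation, because baseline looks back to before the appointment, later scores follow it, and no arm goes without meditation. This follows from the design whatever the frequency of treatment changes. Its size does depend on that frequency: a spurious within-arm fall of 0.4 to 1.2 points for shares of 20% to 60% and an assumed 2-point mean response.

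The between-arm comparison remains valid and pays in precision: at a 40% share, SD 2.49 instead of 2.20 and power 0.43 instead of 0.52 for a 1-point effect. Every input to these figures other than 39 per arm is an assumption; if few patients have a change at T1, the loss is small.

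**What to change.** 1. On the existing T1 clinical questionnaire, before randomization, record (a) first consultation or established patient, and (b) whether analgesic or anticancer treatment was changed at that day's appointment or within a fixed preceding window (yes/no). The article differs on whether this questionnaire is repeated at T2 and T3 (Section 2.5 says so, Table 2 lists it at T1 only), but T1 is common to both.
2. Use item (b) as a prespecified baseline covariate in the primary between-arm model. In a repeated-measures or GEE model, include its interaction with time, because it predicts change and not only level.
3. Reword Sections 3.2 and 5 so that conclusions rest on between-arm contrasts and within-arm change is descriptive only.

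The cost is two questionnaire items and one covariate. The gain in precision depends on how common such changes prove to be and how accurately they are recorded. No patient's treatment is affected, and no stability window is proposed, since it would trade recruitment for homogeneity in a setting where recruitment is already limited.

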### 2.2. Study Setting

This project was approved on 5 January 2024 by the FCECON Research Ethics Committee under the number CAAE: 76043823.0.0000.0004 and subsequently registered on the following Research Registration Platforms: Brazilian Registry of Clinical Trials (ReBEC) under number 15,398 and ClinicalTrials.gov/NCT06328751/Universal Trial Number (UTN) number U1111-1304 3752.

The research is conducted in the medical office, used by the medical team to care for patients monitored by the Pain Therapy and Palliative Care Service (STDCP) of the Amazonas State Oncology Center Foundation (FCECON). The STDCP has a multidisciplinary team of anesthesiologists specializing in pain therapy, palliative medicine, and acupuncture, nurses, psychologists, physical therapists, chaplains, and nursing technicians. All research processes are carried out in rooms used by the STDCP team and conducted by the team responsible for the protocol. This team includes doctors and medical students trained to explain all phases of the study, its risks, and its benefits; ensure confidentiality before, during, and after the research; and provide compensatory assistance to those who suffer harm from participating in the study.

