## Figures and Tables

**Figure 1 healthcare-14-00266-f001:**
[figure not shown]
Flowchart of the experimental design.

**Table 1 healthcare-14-00266-t001:** Temporal implementation of the experimental protocol.

Planning (0–1 Year)	Intervention (1–2.5 Years)
Questionnaire preparation Definition of criteria Patient selection Randomization and sample size Group allocation	Informed consent (TCLE) Initial questionnaire Assessments at 3 time points Meditation protocol Edmonton Symptom Scale

**Table 2 healthcare-14-00266-t002:** Descriptive table of the experimental groups; time of the experimental protocol; and instruments applied.

Group	Time	Study Assessment Instruments
Case group (Group A) Virtual reality/3D (VR)	Time 1 (T1)—First Day of Intervention	
	Before Meditation	Sociodemographic and clinical questionnaire McGill Quality of Life Questionnaire [17] Brief Pain Inventory (Short Form) [18] Hospital Anxiety and Depression Scale [19] The Edmonton Symptom Assessment Scale (ESAS) [20] The National Comprehensive Cancer Network^®^ (NCCN) [21]
	After Meditation	The Edmonton Symptom Assessment Scale (ESAS) [20]
Active Control Group (Group B) Guided Meditation 2D Video	Time 2 (T2)—Four Weeks After T1	
	Before Meditation	McGill Quality of Life Questionnaire [17] Brief Pain Inventory (Short Form) [18] Hospital Anxiety and Depression Scale [19] The Edmonton Symptom Assessment Scale (ESAS) [20] The National Comprehensive Cancer Network^®^ (NCCN) [21]
	After Meditation	The Edmonton Symptom Assessment Scale (ESAS) [20]
Passive Control Group (Group C) Audio-guided meditation—Audio for breathing exercises	Time 3 (T3)—Eight Weeks After T1	
	Before Meditation	McGill Quality of Life Questionnaire [17] Brief Pain Inventory (Short Form) [18] Hospital Anxiety and Depression Scale [19] The Edmonton Symptom Assessment Scale (ESAS) [20] The National Comprehensive Cancer Network^®^ (NCCN) [21]
	After Meditation	The Edmonton Symptom Assessment Scale (ESAS) [20]

**Table 3 healthcare-14-00266-t003:** Overview of outcome measures and analytical framework.

Outcome	Measurement Variable	Analysis Metric	Aggregation Method	Time Points
Primary outcome	BPI: “worst pain in the last 24 h” (0–10)	Change from baseline; final value	Mean (SD); mean difference	T1, T2, T3
Psychological morbidity	HADS total and subscales	Change from baseline	Mean (SD)	T1, T2, T3
Quality of life	McGill Quality of Life Questionnaire scores	Change from baseline	Mean (SD)	T1, T2, T3

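### The plan gives the research team access to the randomization sequence and states no rule that hides upcoming assignments, so allocation concealment is not protected

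*Protocol article*

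**What the plan says.** Four parts of the protocol article bear on this.

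- **Access to the sequence.** Section 2.5: "The randomization sequence and the type of meditation used in each group at the FCECON office are accessible to the research team". The sentence goes on to contrast this with participants, who are not told about the other groups.
- **Who does the work.** Section 2.2: "All research processes are carried out in rooms used by the STDCP team and conducted by the team responsible for the protocol". On the make-up of the team: "This team includes doctors and medical students trained to explain all phases of the study, its risks, and its benefits".
- **Who randomizes, and how.** Section 2.5.4: "The randomization is performed by the principal investigator using a specific commercial mobile application". The article calls the app secure and validated, and the protection it describes is that it "works with encrypted network traffic using TLS (Transport Layer Security), a strong encryption for random distribution among the research groups". The same section says that the questionnaires are given by researchers who know the intervention modality, that the statistician is blinded, and that the unblinded evaluator is a limitation.
- **Order of steps.** Table 1 lists, under the planning phase (0–1 year), "Patient selection Randomization and sample size Group allocation". Informed consent and the initial questionnaire stand under the later intervention phase (1–2.5 years). Section 2.3 makes consent a condition of taking part but does not place it before randomization.

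**The concern.** Concealment and blinding are different protections. Blinding concerns who knows the arm after assignment, and with a headset, a video and an audio recording it is largely out of reach here. Concealment concerns whether anyone who decides on entry can know the next arm before that decision is final. It is achievable in an open-label trial, and it matters more there because fewer other safeguards remain.

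If a recruiter can see the next assignment, a patient thought likely to do well or badly can be steered in, deferred or excluded according to the arm. The groups may then differ at entry for reasons other than chance. The primary outcome is the self-reported change in worst pain from T1 to T3, so both the type of patient entered and the way the baseline is elicited could affect the comparison. A statistician who sees only coded labels cannot detect or undo this.

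**Working it through.** No arithmetic applies. The point does not depend on the effect size, alpha, power, dropout or the 43 participants per group, and correcting it changes none of them. The check sets the statements side by side.

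1. **Is the sequence open?** Section 2.5 says that it is accessible to the research team. The object is the sequence, not only a participant's own assignment, and no role or moment (such as after enrolment) limits the access. This is a positive statement, not a detail left out of a condensed article. A fuller protocol could explain it, but the sentence as it stands is not compatible with concealment.

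2. **Does that team meet patients before entry?** Section 2.2 has the protocol team conduct all research processes, and its doctors and medical students explain the study. No section names a recruiter, so it is an inference that those who enrol can see the sequence. It is a strong one, because no separate recruiting staff and no independent holder of the sequence are described.

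3. **Is there room for judgement at entry?** Yes. Section 2.3 excludes patients for "impaired comprehension and communication skills based on the" researcher's own view of the patient. A criterion of that kind can be applied differently when the next arm is known.

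4. **Does any stated safeguard close the gap?** Encrypted traffic protects data in transit; it does not hide the next assignment from the person using the app. The principal investigator operates the app, and the article does not say whether that person also enrols. The blinded statistician works after enrolment. The limitation that the authors admit is the unblinded evaluator, not the open sequence.

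5. **Is the order of steps fixed elsewhere?** No. Section 2.4 places all questionnaires before the meditation session at each visit, but before the session is not the same as before assignment. Section 2.5.4 has them administered by staff who know the modality, without saying that the T1 baseline comes before assignment. Table 1, read literally, puts allocation first. No section states the sequence of eligibility, consent, baseline and assignment.

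Steps 1 to 4 carry the finding. Step 5 shows that the rest of the article does not rescue it.

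**The case against.** The best reply is that the sentence in section 2.5 belongs to a paragraph on who knows what. It may mean only that staff know assignments once made, which section 2.5.4 says again. The article does not say that the app shows a forward list. This stands as a limit on the conclusion: the document does not show that concealment failed in practice. It does not remove the point, because the text names the sequence, grants access without limit and gives no rule the other way.

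Three stronger readings are tempting and are not supported:

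- **Allocation precedes consent.** A reader might infer this from Table 1. But the table is a two-column project timeline whose planning column also holds set-up work such as questionnaire preparation and sample size. It may mean preparing the randomization. Taken literally, it would also fit poorly with section 2.5, where T1 data are collected straight after the medical appointment. It is ambiguous, not proof.
- **The baseline pain score is collected by staff who already know the arm.** This is possible under the text, but not shown. It depends on the order of steps, which is not stated.
- **Clinic days reveal the arm.** Section 2.5 does say "Data collection takes place separately on different days and at different times", but the purpose given is to keep one participant from another's meditation. Nothing links days to groups.

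It is also fair to say that interviewer bias is a matter of assessor blinding, which the authors already concede. The point here is access to the sequence before entry, which they do not mention.

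**Conclusion.** The point holds in this form: the article states open access to the sequence for the team that conducts all research processes, and nowhere says that upcoming assignments are hidden until enrolment. As written, concealment is not protected and selection at entry is possible. Confidence is high for what the text says. It is lower for what happens in practice, since the recruiter, the app's display and the order of steps at T1 are not described. The conclusion assumes that the people who explain the study and judge eligibility are among those with access.

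The size of any bias cannot be estimated from the document, and a figure in pain-scale points would rest on invented inputs. The point still needs correction before the between-group comparison can be relied on, because later analysis cannot fully restore what concealment protects.

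**What to change.** - Replace the sentence in section 2.5 with a rule that upcoming assignments are not visible to anyone who screens, obtains consent or interviews.
- State the order at T1 in section 2.5.4: eligibility confirmed, consent signed, all pre-meditation T1 questionnaires completed, and only then the app releases that one participant's arm.
- Clarify Table 1 so that preparing the randomization stays under planning, while individual allocation follows consent and the initial questionnaire.
- If participants were already enrolled with an open sequence, say so and report it as a limitation next to the unblinded evaluator. New wording cannot restore concealment for them.

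The cost is small: revised wording and a changed order of steps at T1, with the app already in use. The team must confirm that the app can keep upcoming assignments from view, since the article does not describe this. If the principal investigator also enrols patients, an existing team member who is not involved in enrolment should operate the app.
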